### Interim analyses {21b}

No detrimental problems to the study participants are anticipated. In addition, conflicts of interest within the decision-making process during the trial’s execution, specifically concerning the reallocation of resources to address unmet needs, are expected. Therefore, no interim analyses are planned.

### Methods for additional analyses (e.g. subgroup analyses) {20b}

Important prognostic variables are centre, sex and gestational age, or main neonatal diagnosis. These will be used as additional independent variables in key secondary logistic regression models for secondary subgroup analysis.

Further subgroup analysis will be conducted in line with the primary analysis, where the endpoint is dichotomous. For continuous endpoints, similar modelling strategies will be used, but instead of logistic regression linear regression models will be used.

The cost-effectiveness analysis of RISEinFAMILY implementation will be carried out using recommended methods [35, 36]. A decision-analytical [37] will be developed and populated with costs and effectiveness data from the pilot studies. For each RISEinFAMILY implementation site, the cost-effectiveness of the intervention will be estimated. The cost-effectiveness and the value of implementation analyses will be conducted for the seven neonatal units involved in the study. The mean net monetary benefit per participant will be calculated using the health care system willingness-to-pay threshold corresponding to the current cost of neonatal care in the NICU.

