### Objectives {7}

The aim of the RISEinFAMILY project is to develop a FICare model adapted to different cultural, architectural and socio-economic contexts as the new international standard for neonatal care and provide sound data on its sustainability based on a cost-effectiveness analysis.

The adapted FiCare model (herein after RISEinFAMILY model) will include a wider geographical and sociocultural diversity and 2 implementation levels (basic and advanced) and will try to demonstrate its superiority, against routine current provision of care, in infants’ clinical outcomes, parental mental health and professional’s self-care and satisfaction.

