For our primary hypothesis, we will compare infant standardised weight gain velocity between the two groups over the 4-week study period using generalised linear mixed modelling (GLMM). For our primary outcome, we will compare infant standardised weight gain between the two groups over the study period defined as the change in Patel’s growth pattern measured weekly from enrolment until day 28 post-enrolment, testing an interaction term between group and post-baseline weight measurements. We will adjust for additional covariates using a hybrid approach, forcing in known confounders of gestational age and study site and using backward stepwise selection to retain covariates that contributed *p* < 0.1 to the final model from potential confounders. Additionally, we will conduct sensitivity analyses by adding in weight measured at discharge.

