It is important to consider the potential variations in the execution of the intervention across different hospitals, particularly regarding the human factors involved, such as the communication and collaborative skills of healthcare professionals. Ultimately, the robust evidence generated from this research will support the implementation of an international FICare package, regardless of architectural, cultural or economic differences. This will lead to improved neonatal care and enhanced outcomes for families and healthcare professionals. The study results are expected to contribute to the existing evidence base and inform future interventions and clinical practices in neonatal care worldwide.

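### The analysis labelled as subgroup analysis only adjusts for centre, sex, gestational age or diagnosis, so it gives one pooled effect and no subgroup effect on clinical, parental or staff outcomes

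*Protocol article*

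**What the plan says.** Section {20b} of the protocol article covers additional and subgroup analyses. It begins: "Important prognostic variables are centre, sex and gestational age, or main neonatal diagnosis". It then gives the method: "These will be used as additional independent variables in key secondary logistic regression models for secondary subgroup analysis". Two more sentences follow: "Further subgroup analysis will be conducted in line with the primary analysis, where the endpoint is dichotomous" and "For continuous endpoints, similar modelling strategies will be used, but instead of logistic regression linear regression models will be used".

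The primary model in section {20a} is a mixed model adjusted by "forcing in known confounders of gestational age and study site". The one interaction it names is described as "testing an interaction term between group and post-baseline weight measurements".

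The Objectives {7} set out to "develop a FICare model adapted to different cultural, architectural and socio-economic contexts". The Discussion expects the evidence to support an international package "regardless of architectural, cultural or economic differences".

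**The concern.** A variable added to a regression as a further independent variable is adjusted for. The intervention still has one coefficient, and that coefficient is assumed to be the same in every centre, in both sexes, at every gestational age and in every diagnosis. A subgroup analysis needs either a product term between intervention and the variable, or an effect estimated within each stratum. Section {20b} states neither, so the method does not do what its label says.

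This matters more here than in most trials, because variation between settings is close to the reason for the study. An analyst who follows the text would produce adjusted pooled effects under a subgroup heading. A reader could then take one average as evidence that the model works in each setting, although the analysis made no comparison of effects between settings.

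**Working it through.** **1. Does any section supply the missing term?**
- {20b}, further subgroup analysis: refers back to the primary analysis. There, site and gestational age are forced in as confounders, and the only interaction is group by post-baseline weight.
- {20b}, continuous endpoints: the same structure with linear in place of logistic regression.
- {20a}, effect of expertise: compares already trained centres with non-experienced ones. Sites 6 and 7 run the intervention from the start ({11a}), so this is not an intervention effect by setting.
- Discussion: mentions an interaction of time, not of setting.
- {20a} and {20b}, economics: cost-effectiveness by site, and differences in delivery between countries. These are the only planned results by setting.

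Nothing supplies an intervention-by-variable term or a stratum-specific effect for clinical, parental or staff outcomes.

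**2. Sample size inputs.** The plan gives no figure for subgroups. Its only sample size is 46 per group ({14}), and that reproduces: n = 2 × (1.96 + 1.645)² × 2.5² / 1.9² = 45 by the normal approximation, and 46 with the t distribution (two-sided 5%, power 95%). The number per site is not stated. The total of 552 in {8} equals 5 × 2 × 46 + 2 × 46, which would fit 46 per site and phase at sites 1 to 5, but this is an inference. The other end of the range is 46 per group spread over five sites: 46 / 5 = 9.2.

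**3. What the stated model returns.** The model is logit(p) = site term + β × group. Assume site log odds ratios of 1.2, 0.8, 0.4, 0 and -0.4, that is, odds ratios of 3.3, 2.2, 1.5, 1.0 and 0.67. Their mean is 0.4, and exp(0.4) = 1.49. Simulation with 46 per site and phase gives a single odds ratio of about 1.47 to 1.49 at a control risk of 50%, and about 1.52 to 1.55 at 38%. The spread from 0.67 to 3.3 does not appear in the output.

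**4. What an interaction term could detect.** Same odds ratios, likelihood-ratio test of group by site on 4 df at 5%:
- 46 per site and phase: power about 34 to 65%, lowest when the control risk is low (10%).
- 9 per site and phase: about 13 to 22%.

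**5. The same on the growth scale** (SD 2.5 g/kg/d from {14}, independent observations, n per arm in each subgroup):
- 95% CI half-width for one site's effect = 1.96 × 2.5 × √(2/n): 1.0 g/kg/d for n = 46 and 2.3 g/kg/d for n = 9.2, against a target effect of 1.9.
- SE of the difference between two subgroup effects = 2.5 × √(4/n): 0.74 and 1.65. Power for a difference of 1.9 is Φ(1.9/SE - 1.96): 73% and 21%.

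These figures ignore clustering, time trend and multiplicity, so they are optimistic.

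**6. What an interaction term could wrongly detect.** Each of sites 1 to 5 crosses once, at a time that was not randomised ({11a}, {16a}, {16c}). With an identical true effect at all sites, 46 per site and phase and a control risk of 40%, site-specific trends of SD 0.3 or 0.5 on the log-odds scale made the group-by-site test significant in about 19% and 40% of simulated datasets. With no trend it was about 6%.

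**The case against.** The best defence is that the article condenses a fuller protocol and that model formulas usually sit in the SAP. The sentence on further subgroup analysis could also be read as repeating the primary comparison within each subgroup. That reading is not in the text. The article does not stay silent on the method either: it commits to a specific one and gives it a label that does not fit.

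Other parts of the defence stand, and they limit the point:
- A reader might infer that the trial can say nothing about settings, or that a site with no benefit or harm would necessarily go unseen. The documents do not support that. Cost-effectiveness is planned for each unit using effectiveness data, and differences in delivery between countries are to be identified. These are not tests of whether clinical, parental or staff effects differ, so the gap is confined to those outcomes.
- A reader might infer that the trial sets out to prove an equal effect at every site. It does not. The Objectives speak of adaptation and of superiority over routine care. The phrase about architectural, cultural or economic differences is an expectation in the Discussion, which also acknowledges that execution may vary between hospitals.
- The site odds ratios and the numbers per site are assumptions, and power depends strongly on control risk. Only a range can be defended.
- A group-by-site term is no clean remedy, as step 6 of the working shows.

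**Conclusion.** The concern holds in this limited form. The method described as subgroup analysis in {20b} is covariate adjustment. It returns one pooled intervention effect, and no other section supplies a subgroup effect for clinical, parental or staff outcomes. For those outcomes the planned analysis cannot inform scalability across contexts. That conclusion follows from the wording alone and rests on no numerical assumption.

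The size is illustrative: under the assumed site odds ratios of 0.67 to 3.3, one odds ratio near 1.5 would be reported. The primary comparison is unaffected. Correcting the wording would make differences between settings visible as estimates, but would not make them confirmatory.

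**What to change.** In {20b}, replace the covariate-only wording with interaction terms between intervention and, one at a time, centre, sex, gestational age and main diagnosis. Fit them in a model with the same clustering structure as the primary analysis, a link suited to the endpoint, and a term for calendar time. Restrict the centre term to sites 1 to 5, because sites 6 and 7 have no control phase. For staff outcomes only the centre term applies. Report subgroup-specific effects with 95% CIs and a forest plot of the five sites, and label all of it exploratory.

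State the limits alongside:
- Intervals will be wide and power low, so absence of a significant interaction is not evidence of a uniform effect.
- Each site crosses once and in non-random order. Its effect is a before-after contrast; a common calendar-time term removes a shared trend but not the site's own.
- With one non-experienced site per country, the term cannot separate culture, architecture and economy.

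The cost is a change of wording and a few extra model runs, with no new data. The Discussion's expectation about differing settings should then be tied to these exploratory estimates.

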**Methods:**

RISEinFAMILY is a pluri-cultural, stepped wedge cluster controlled trial conducted in Spain, Netherlands, the UK, Romania, Turkey, and Zambia. Eligible participants include infant-family dyads admitted to the Neonatal Intensive Care Unit (NICU) requiring specialised neonatal care for a minimum expected duration of 7 days, provided there are no comprehension barriers. Notably, this study will incorporate a value of implementation analysis on FICare, which can inform policy decisions regarding investment in implementation activities, even in situations with diverse data.

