### Outcomes {12}

The study’s primary outcomes are as follows: (a) RISEinFAMILY implementation: proportion of families completing basic and advanced training levels (observed vs expected), average time to complete basic and advanced training levels (observed vs expected) and average time of kangaroo care per day (hours); (b) short-term health infant’s outcomes: proportion of high-risk infants achieving and maintaining adequate growth patterns during NICU admission, defined according to Patel’s method [10, 11].

The study’s secondary outcomes are as follows: reported adverse event rate per 1000 patients/day, feeding patterns and major morbidities at 36 weeks postmenstrual age (PMA) or discharge, nosocomial infection [12], necrotising enterocolitis (Bell’s > stage 2), moderate-severe brain injury (worst cranial ultrasound) [13], parental needs, empowerment and psychological health (stress [14], anxiety and depression [15, 16], self-efficacy [17], bonding [18], resilience [19]), professional’s self-care and satisfaction (anxiety and depression [15], burnout [20], post-traumatic stress [21], work and well-being [20]).

The study’s exploratory outcomes are as follows: economic impact (level of post-implementation utilisation of FICare, resources and costs associated with FICare implementation, cost-effectiveness estimates compared to the current care, expected value of current implementation and expected value of perfect implementation); mid-term infant’s general health (growth pattern during the first 12 months from birth, use of health system facilities after discharge); long-term neurodevelopment (survival without neurodevelopmental disabilities).

Specific items and test batteries are stated in Additional file 1.

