## Statistical methods

### Statistical methods for primary and secondary outcomes {20a}

The primary analysis will be conducted in the intention-to-treat (ITT) population including all enrolled patient-family dyads who received at least one task training according to protocol procedures.

Descriptive statistics will be recorded for each group with mean, median and standard deviation for numerical variables and absolute and relative frequencies for categorical variables. 95% confidence intervals (CIs) will be provided. Comparisons between control and intervention groups will be performed using chi-square tests for categorical variables, analysis of variance for normally distributed continuous variables, and Mann–Whitney or Kruskal–Wallis tests for non-normally distributed continuous variables. Through a mixed-methods research approach and techniques both quantitative and qualitative, the following impacts will be evaluated: (a) effect of intervention: the control and the intervention group dataset from the non-FICare-experienced centres will be compared; (b) effect of “expertise” on outcomes: comparisons will be conducted between datasets from already trained FICare centres and those from the non-FICare-experienced centres.

Socio-economic sustainability: Health economics analysis based on the value of implementation framework will be conducted to assess the cost-effectiveness of RISEinFAMILY implementation strategies. The difference between the total net benefit of perfect adoption and the total net benefit of current implementation will generate the expected value of perfect implementation (positive values would characterise cost-effective implementation strategies). The analysis will also allow identifying differences in delivering RISEinFAMILY in different countries/health care settings.

Psychological assessment of experiences collected by either the NICUs staff and the families enrolled in the pilots will be conducted. Gender differences will be explored in relation to socioeconomic and cultural background.

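### The net monetary benefit threshold is tied to what NICU care now costs, so the price put on a health gain rises with existing spending instead of reflecting the payer's value for that gain

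*Protocol article*

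**What the plan says.** The rule is in the protocol article under Methods for additional analyses {20b}. It says "The mean net monetary benefit per participant will be calculated", and that this will be done "using the health care system willingness-to-pay threshold corresponding to the current cost of neonatal care in the NICU". In the same paragraph, "For each RISEinFAMILY implementation site, the cost-effectiveness of the intervention will be estimated", and "The cost-effectiveness and the value of implementation analyses will be conducted for the seven neonatal units involved in the study". The abstract lists six countries, from the Netherlands and the UK to Zambia.

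Under Statistical methods for primary and secondary outcomes {20a}, net benefit feeds the value-of-implementation result. "The difference between the total net benefit of perfect adoption and the total net benefit of current implementation" gives the expected value of perfect implementation, and "positive values would characterise cost-effective implementation strategies".

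Outcomes {12} places the economic results, including "cost-effectiveness estimates compared to the current care", among the exploratory outcomes. Objectives {7} nevertheless makes sustainability, judged by cost-effectiveness, part of the project's aim. Nowhere does the article state a different threshold.

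**The concern.** Net monetary benefit multiplies the health effect by a threshold and subtracts the extra cost. The threshold turns health into money, so it has to be money per unit of health effect, as the payer values it. The current cost of NICU care is money per infant or per day of care. It describes the comparator's resource use and already has a place in the cost term.

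The article does not leave the threshold open for a later plan; it fixes it, and fixes it to the wrong kind of quantity. The affected results are the per-participant net benefit at seven units and the value-of-implementation result built on it. Section {20a} also intends to compare delivery across countries and care settings. Part of any difference found would come from the threshold rule itself.

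**Working it through.** There is no figure in the plan to reproduce: the article gives no threshold, economic effect or cost. All numbers below are assumed, to show how the rule behaves.

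**Notation.** dE = incremental effect, dC = incremental cost, L = threshold, NMB = L × dE − dC. Break-even is L = dC / dE.

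**1. Price put on the same gain.** Take dE = 0.15 infants with adequate growth. The rule sets L to current NICU cost per infant.
- Cost 40,000: 0.15 × 40,000 = 6,000.
- Cost 2,000: 0.15 × 2,000 = 300.

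The ratio is 20, equal to the ratio of the existing costs (40,000 / 2,000). This step needs no assumption about dC.

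**2. Net benefit with the same extra cost everywhere.** With dC = 1,000, break-even is 1,000 / 0.15 = 6,667.
- Cost 40,000: 6,000 − 1,000 = +5,000.
- Cost 2,000: 300 − 1,000 = −700.

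With dE = 0.05 and dC = 1,000, break-even is 20,000. NMB is −900 at a cost of 2,000, −500 at 10,000, 0 at 20,000, +1,000 at 40,000 and +3,000 at 80,000. With dE = 0, NMB is −1,000 at every threshold, so the effect does still matter.

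**3. Net benefit with extra cost proportional to local cost.** Let dC be 2.5% of NICU cost (1,000 of 40,000; 50 of 2,000).
- Cost 40,000: +5,000.
- Cost 2,000: 300 − 50 = +250.

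The sign no longer changes, so a reversal depends on how dC is assumed to vary. The twentyfold difference in the price of the gain remains. Dividing NMB by current cost C (with L = C) gives dE − dC / C, here 0.15 − 0.025 = 0.125. The rule therefore asks whether the effect exceeds the fractional rise in NICU cost. No payer valuation of health appears in that test.

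**4. Value of implementation.** Let N be the eligible infants, u the current uptake, and leave aside the cost of raising uptake. Perfect adoption gives N × NMB and current implementation gives N × u × NMB. The difference is N × (1 − u) × NMB, so both the sign and the distortion of NMB carry over.

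**5. The reading in which units match.** Suppose the effect is NICU days saved and L is cost per NICU day: 3 days at 1,500 gives 3 × 1,500 = 4,500. Implementation cost is 1,000.
- Cost term holds implementation cost only: NMB = 4,500 − 1,000 = 3,500. This is a plain saving, with no value placed on growth or any other health gain.
- Cost term also includes the stay: dC = 1,000 − 4,500 = −3,500, so NMB = 4,500 + 3,500 = 8,000. The saved days count as 9,000 where 4,500 was saved.

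**The case against.** The strongest defence is that days saved, priced at cost per day and set against implementation cost, form a coherent net benefit that counts nothing twice. The background stresses shorter stay, and Outcomes {12} lists implementation resources and costs. This stands in part: double counting is conditional on the cost term including the stay, and the article does not settle that. But the reading is not stated, and if it is what was meant, the analysis measures savings only.

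A reader might also infer several stronger points that the article does not support:
- *The health gain is ignored.* It is not. The effect multiplies the threshold; what the rule replaces is its price.
- *Each unit is judged by its own cost.* The wording refers to a health-care-system threshold, which may be one value per country. Estimating cost-effectiveness by site does not imply a site-level threshold. The dependence on existing cost remains across six countries either way.
- *Sites will receive opposite verdicts.* That depends on the assumed costs, as step 3 shows. Thresholds set properly for each country can also give different verdicts, so variation between countries is not in itself evidence of error. The fault lies in what sets the threshold.
- *The article should have named the effect unit, a threshold range or acceptability curves.* Those details may well be in the full protocol, the additional file or a health-economics plan, none of which is shown. Their absence here is not a finding.

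Finally, the analysis is said to follow recommended methods. That general statement does not displace a specific sentence that fixes the threshold.

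**Conclusion.** The point holds at moderate severity. The article sets the threshold from a cost input, so the price of a given health gain scales one for one with existing NICU cost: twentyfold between assumed costs of 40,000 and 2,000. That follows from the rule alone when the threshold is taken as cost per infant. The sign of net benefit, and any double counting, rest on further assumptions about the cost term that the article does not give.

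The effect is confined to the economic results, which are exploratory. The growth and implementation outcomes, the sample size and data collection are untouched. It still merits correction because Objectives {7} promises sound sustainability data from this analysis and the abstract expects it to inform investment decisions.

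**What to change.** In section {20b}, delete the clause that ties the threshold to current NICU cost. Replace it with text to this effect: *Net monetary benefit will use each health system's external willingness-to-pay threshold per unit of the chosen health effect, where one exists. Where none exists, the incremental cost-effectiveness ratio will be reported, with net monetary benefit over a pre-stated range of thresholds. The cost of NICU care will enter only the cost term.* In section {20a}, say that the expected value of perfect implementation uses these same thresholds.

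If NICU days saved are to be valued at cost per day, report that separately as a cost-saving analysis, with the days counted once.

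The cost is a little more economic analysis and, where a range is used, less of a single verdict per site. No new data are needed.
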